**“Intervention” (different modalities of renal replacement therapy, chosen by the patient, are observed):**

Group A: treatment with frequent nocturnal hemodialysis;

Group B: treatment with renal transplantation;

Group C: continuous treatment with hemodialysis;

Group D: continuous treatment with peritoneal dialysis.

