## 1. INTRODUCTION AND RATIONALE

Cardiovascular disease (CVD) is the leading cause of death in patients with end-stage renal disease (ESRD). From several perspectives, the pathophysiology of ischemic cardiovascular events is different in ESRD compared to the general population. In patients with ESRD, the classical risk factors for CVD, such as hypertension, obesity and hyperlipidemia are associated with decreased mortality instead of increased mortality ("reverse epidemiology"). Vascular calcification appears to be the central finding in the pathophysiology of CVD, manifesting itself in increased arterial stiffness and mediasclerosis. The presence and extent of vascular calcifications are strong predictors of all-cause and cardiovascular mortality in hemodialysis patients, independent of classical atherogenic factors.

Elevated calcium and phosphate concentrations or loads in the serum of ESRD patients have direct effects on vascular smooth muscle cells that induce an osteogenic "bone-like" differentiation of these cells. Reducing the calcium concentration in ESRD patients by the prescription of non-calcium-containing phosphate binders can slow down the progression rate of arterial calcification. Coronary artery calcification in young hemodialysis patients is strongly associated with dialysis vintage, calcium-phosphorus-product and oral calcium load.

It has been well documented that correction of calcium and phosphorus parameters is also possible by means of long and frequent hemodialysis, such as nocturnal hemodialysis. A single short-term study on nocturnal hemodialysis showed stabilization of coronary artery calcification score, but comparison with renal transplantation and conventional hemodialysis and peritoneal dialysis was not made. Therefore this study aims to compare the progression of coronary artery calcification score in 4 models of treatment of ESRD: conventional hemodialysis, peritoneal dialysis, renal transplantation and nocturnal hemodialysis.

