## **4. STUDY POPULATION**

### **4.1 Population**

The study populations consists of 4 cohorts of patients: patients who start with frequent nocturnal hemodialysis, patients who receive a renal transplant and 2 control groups treated with hemodialysis and with peritoneal dialysis. The study is sponsored by Dianet Dialysis Centers, while all research activities take place in University Medical Center Utrecht. Patients were screened at their local treatment facility (Dialysecentrum Groningen, Groningen; Dialysecentrum Diapriya, Amsterdam; VU medisch centrum, Amsterdam; Meander Medisch Centrum, Amersfoort; Rijnstate Ziekenhuis, Arnhem; Sint Antoniusziekenhuis, Nieuwegein; Stichting Dianet Dialysecentra, Utrecht and Amsterdam; and University Medical Center Utrecht, Utrecht), and if interested in the study, subsequently referred to University Medical Center Utrecht for study participation.

- 40 patients who start treatment with frequent nocturnal hemodialysis are asked to participate in the study;
  - 40 patients who receive a renal transplant, after having been treated with hemo- or peritoneal dialysis, are asked to participate in the study;
  - 40 patients who are treated with conventional hemodialysis are asked to participate; in order to enhance similarity between groups only hemodialysis patients are recruited that are or could be eligible to be on the waiting list for renal transplantation;
  - 40 patients who are treated with peritoneal dialysis are asked to participate; in order to enhance similarity between groups only peritoneal dialysis patients are recruited that are or could be eligible to be on the waiting list for renal transplantation.
- Groups will be matched according to age, sex, presence of diabetes mellitus and duration of dialysis, in order to minimize between-group differences to 25% regarding these factors.

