### **4.4 Sample size calculation**

The effects of the different modalities of renal replacement therapy on arterial calcification are analyzed with linear regression, after transformation of calcium scores. The effects of risk

factors for calcification, including inflammation parameters and calcification inhibitors are analyzed in a multivariate model. The mean ( $\pm$ SD) coronary calcification score in ESRD patients is 2370 ( $\pm$  352). The multislice CT-scan is extensively validated in our institute. At this level of calcification the variation between independent measurements is less than 10%. Therefore we can demonstrate an increase or decrease in calcification score of 15%, in 4 subpopulations of 22 patients with ESRD, with a type I error probability for a two sided test of 0.05 and a power of 0.90 [formula: " $N = (2(Z_{\alpha} + Z_{\beta})^2 \cdot sd) / (0.15 \cdot \text{mean})$ " where N = number of patients per group,  $Z_{\alpha} = 1.96$ ,  $Z_{\beta} = 1.28$ ,  $S = 3.52$ , mean = 2370]. To account for a dropout of patients by renal transplantation, switch to a different treatment modality, refusal of further participation or death we intend to include 40-55 patients per group – depending on the dropout, aiming to obtain complete study data in 22 patients per group.

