## **9. STATISTICAL ANALYSIS**

### **9.1 Descriptive statistics**

The population characteristics are described with a categorical or continuous output, as appropriate.

The primary endpoint, coronary artery calcification score, is a continuous variable with a skewed distribution, and will be presented with its median and ranges. Progression of calcification score will be analyzed with multinomial logistic regression, dividing the coronary artery calcification score in three categories. The same goes for pulse wave velocity of the aorta and iliac arteries.

The calcification score of the different groups will be compared by regression analyses.

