### **9.2 Univariate analysis**

The relation between each independent variable (demographic data, calcium-phosphate parameters, inflammation markers and calcification inhibitors), and primary outcomes will be determined with univariate linear regression analysis. The relationship between these independent variables and secondary outcomes (change in coronary calcification score, change in pulse wave velocity) will be determined with univariate linear regression analysis. Because the relative change in calcification score can be independent from the initial absolute calcification score, the results will be corrected for initial calcification score.

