### **9.3 Multivariate analysis**

The effects of age, gender, body weight, blood pressure, medication, hemoglobin, lipids, quality-of-life, performance status and medication on the relation between each independent variable (demographic data, calcium-phosphate parameters, inflammation markers and calcification inhibitors), and primary outcomes will be determined with multivariate linear regression analysis. The effects of age, gender, body weight, blood pressure, medication, hemoglobin, lipids, quality-of-life, performance status and medication on the relationship between these independent variables and secondary outcomes (change in coronary calcifications score, change in pulse wave velocity) will be determined with multivariate linear regression analysis.

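### No planned model adjusts the comparison of self-chosen modalities for all four matching factors: the covariate list in 9.3 omits diabetes and dialysis duration, leaves out modality as an exposure, and fixes no time point

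*Protocol*

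**What the plan says.** The Summary describes the exposure thus: "different modalities of renal replacement therapy, chosen by the patient, are observed". Section 7.2 confirms that there is no randomization.

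Section 4.1 matches the cohorts on age, sex, "presence of diabetes mellitus and duration of dialysis, in order to minimize between-group differences to 25% regarding these factors". It does not say whether 25% is absolute or relative.

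The modality comparison is described in two places. Section 4.4: "The effects of the different modalities of renal replacement therapy on arterial calcification are analyzed with linear regression, after transformation of calcium scores". Section 9.1: "The calcification score of the different groups will be compared by regression analyses". Section 9.1 also mentions a multinomial model for progression in three categories. None of these names a covariate.

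Section 9.2 deals with univariate risk-factor analyses and adds that "the results will be corrected for initial calcification score".

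Section 9.3 gives the only covariate list: "The effects of age, gender, body weight, blood pressure, medication, hemoglobin, lipids, quality-of-life, performance status and medication on the relation between each independent variable". Those independent variables are demographic data, calcium-phosphate parameters, inflammation markers and calcification inhibitors. Modality is not among them.

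On dialysis duration, the Introduction says that coronary calcification in young hemodialysis patients "is strongly associated with dialysis vintage, calcium-phosphorus-product and oral calcium load". It also expects patients with a long period on dialysis to be among those who progress fastest.

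**The concern.** In a non-randomized comparison, confounding control has to come from the design, the analysis or both. The design part here is matching with a stated tolerance, so imbalance inside that tolerance is left to the analysis. The protocol then sets out a covariate list that covers two of its own four matching factors and drops the other two. One of the dropped factors is dialysis duration, which the Introduction ties to the outcome.

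The list is also not attached to the primary question, because modality is not an exposure in 9.3. Most of its items are variables that modality can alter and that are measured repeatedly, with nothing said about which measurement enters. An analyst who follows section 9 literally would report a modality effect with no named protection against differences in diabetes or dialysis duration. An analyst who carries the 9.3 list over to modality would still lack those two factors, and might bring in follow-up values that lie between modality and outcome.

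**Working it through.** **1. Matching factors against the 9.3 list**

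| Factor matched in 4.1 | Named as covariate in 4.4 or 9.1 | On the 9.3 list |
|---|---|---|
| Age | no | yes |
| Sex | no | yes |
| Diabetes | no | no |
| Dialysis duration | no | no |

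The 9.3 list has nine distinct items (medication appears twice). Age and gender cannot be changed by modality. The other seven can: body weight, blood pressure, medication, hemoglobin, lipids, quality of life and performance status.

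**2. Time points.** The investigations table in section 3 and section 7.3 schedule these seven at inclusion and again in follow-up. Section 9.3 does not choose between them. By section 5.1, the nocturnal and transplant groups enter at the start of their modality, so their inclusion values can be pre-treatment. The conventional hemodialysis and peritoneal dialysis groups are described in 4.1 as patients already being treated, so their inclusion values may already reflect the modality.

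**3. The protocol's own sample size.** Inputs from 4.4: mean 2370, SD 352, difference 15%, two-sided 0.05, power 0.90.

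- Difference: 0.15 × 2370 = 355.5, which is 355.5/352 = 1.01 SD.
- Standard formula: 2 × (1.96 + 1.28)² × (352/355.5)² = 20.6, so 21 per group.
- t-test power is 0.891 at 21 and 0.905 at 22. The stated 22 per group is reproduced.

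**4. Illustrative size, one factor.** The protocol gives no effect of diabetes on progression, so 0.5 to 1.0 SD is an assumption. The imbalance is taken as fully used.

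- Bias (in SD) = imbalance × effect.
- Non-centrality = bias × √(22/2).
- Two-sided rejection of a true null = Φ(−1.96 + nc) + Φ(−1.96 − nc).

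| Reading of 25% | Imbalance | Effect (SD) | Bias (SD) | nc | Rejection |
|---|---|---|---|---|---|
| Percentage points | 0.25 | 0.5 | 0.125 | 0.41 | 7.0% |
| Percentage points | 0.25 | 1.0 | 0.25 | 0.83 | 13.2% |
| Relative, prevalence 20% (assumed) | 0.05 | 0.5 | 0.025 | 0.08 | 5.1% |
| Relative, prevalence 30% (assumed) | 0.075 | 1.0 | 0.075 | 0.25 | 5.7% |

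Under the percentage-point reading the bias is 0.125/1.01 to 0.25/1.01, or 12 to 25% of the design difference. The SD used is that of the score, not of its change, so these figures show scale only.

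**5. Feasibility of adjustment.** Completers: 4 × 22 = 88. Model terms: three for modality plus five covariates (baseline score, age, sex, diabetes, dialysis duration) = 8. With an intercept, 88 − 9 = 79 residual degrees of freedom remain.

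**The case against.** The strongest reply is that silence is not a plan. A reader might infer from 9.1 that the groups will be compared without adjustment, but the section says only that regression will be used. A regression with baseline confounders fits that wording, and the covariates of a group model are often left to a statistical analysis plan. This stands. The point therefore rests on the list that 9.3 does fix, which omits two of the protocol's own matching factors.

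A reader might also infer that 9.3 adjusts the modality effect for post-treatment variables and so removes part of it. The documents do not support that. All seven modality-sensitive items are also measured at inclusion, and the 9.3 model does not contain modality, so it cannot strip anything from a modality effect. What remains is that the time point is open.

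Third, controls do exist. Diabetes and dialysis duration are matched on, 9.2 corrects for the initial score, and the objective is worded as association. But the matching has a declared tolerance, and the 9.2 correction is written for the risk-factor analyses. An association meant to compare modalities still needs confounding control.

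Fourth, the error rates depend on an assumed effect and on how 25% is read. This stands, and the relative reading gives rates close to nominal.

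Finally, 4.1 limits the conventional hemodialysis and peritoneal dialysis groups to patients who are or could be eligible for the transplant waiting list, and states no such limit for the nocturnal group. A reader might conclude that the nocturnal group contains ineligible patients. No section says so, and the Summary and sections 7.4 and 7.5 expect transplantation in all three dialysis groups.

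**Conclusion.** The point holds as a gap in confounding control for the primary comparison. Modality is self-chosen, matching tolerates differences of up to 25%, and no planned model adjusts modality for all four matching factors. Section 9.3 omits diabetes and dialysis duration, does not treat modality as an exposure, and leaves open when modality-sensitive covariates are measured.

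The consequence is possible residual confounding of the modality effect by known factors. Its size cannot be derived from the protocol. Under the stated assumptions, the false-positive rate from diabetes imbalance alone ranges from near nominal (about 5.1 to 5.7%, relative reading) to about 7 to 13% (percentage-point reading). The omission itself can be checked in the text and does not depend on these figures. The documents do not establish that the comparison will be unadjusted, or that it will be over-adjusted.

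**What to change.** State in 9.1 and 9.3 that the primary modality comparison is adjusted for baseline transformed calcification score, age, sex, diabetes and dialysis duration, all as recorded at inclusion. Add that follow-up values of body weight, blood pressure, medication, hemoglobin, lipids, quality of life and performance status do not enter that model and are kept for separate association analyses. It would help to say in 4.1 whether the 25% tolerance is absolute or relative.

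The cost is a change of wording in section 9 and five covariate degrees of freedom among about 88 completers. The matching already requires age, sex, diabetes and dialysis duration to be known, and the baseline score is the inclusion scan. Repeating the comparison in waiting-list-eligible patients only is optional; it would need eligibility to be recorded in the nocturnal group.

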### **9.2 Univariate analysis**

The relation between each independent variable (demographic data, calcium-phosphate parameters, inflammation markers and calcification inhibitors), and primary outcomes will be determined with univariate linear regression analysis. The relationship between these independent variables and secondary outcomes (change in coronary calcification score, change in pulse wave velocity) will be determined with univariate linear regression analysis. Because the relative change in calcification score can be independent from the initial absolute calcification score, the results will be corrected for initial calcification score.

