**Main study parameters/endpoints:**

1. Change in coronary artery calcification score, per patient;
2. Change in pulse wave velocity, per patient.

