## **7. METHODS**

### **7.1 Study endpoints**

#### 7.1.1 Main study endpoint

The primary endpoint of the study is:

- change in coronary artery calcification score

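### The protocol does not fix one scale or one model for the primary outcome, and baseline correction is not stated for the cohort comparison

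*Protocol*

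**What the plan says.** - **Summary, main study parameters:** "Change in coronary artery calcification score, per patient". No scale is given.
- **7.1.1:** the primary endpoint is "change in coronary artery calcification score". Again no scale is given.
- **4.4:** the effects of treatment modality "are analyzed with linear regression, after transformation of calcium scores". The transformation is not named. The section then states that "we can demonstrate an increase or decrease in calcification score of 15" percent, with 22 patients per group, two-sided alpha 0.05 and power 0.90. The inputs are a mean score of 2370 and an SD of 352.
- **9.1:** the primary endpoint is here the score itself, which "is a continuous variable with a skewed distribution, and will be presented with its median and ranges". Progression is to be "analyzed with multinomial logistic regression, dividing the coronary artery calcification score in three categories". The cohorts are then compared by regression analyses of no stated type, outcome scale or covariates.
- **9.2 and 9.3:** linear regression of primary outcomes, which are not named, and of secondary outcomes, among which the change in calcification score is listed. No transformation is mentioned. The listed predictors are demographic data, calcium-phosphate parameters, inflammation markers and calcification inhibitors; modality is not among them. Only 9.2 corrects for the initial score, on the ground that "the relative change in calcification score can be independent from the initial absolute calcification score".

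**The concern.** A later analysis plan can name a transformation, but it cannot follow sections that disagree. Section 4.4 makes the outcome continuous and transformed, 9.1 makes it categorical, and 9.2 and 9.3 make it an untransformed change that is listed as secondary.

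The 9.2 rationale adds to the uncertainty. If relative change does not depend on the initial score, relative change needs no correction. It is then absolute change that grows with the initial score and needs it. The reader cannot tell which change is meant.

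This matters more here than in a randomised trial. Patients choose their modality (Summary), there is no randomisation (7.2), and 4.1 matches on age, sex, diabetes and duration of dialysis, with differences of up to 25% tolerated, but not on baseline calcification. Section 1 expects age and time on dialysis to drive progression, so unequal baseline scores are plausible. With a skewed score, the scale and the baseline covariate can then affect both the power and the conclusion on the primary objective.

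**Working it through.** **1. The protocol's own figure.** Inputs from 4.4: mean 2370, SD 352, effect 15%, z-values 1.96 and 1.28.

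- Effect: 0.15 × 2370 = 355.5 score units.
- Usual formula: 2 × (1.96 + 1.28)² × (352/355.5)² = 20.6, so 21 per group. The t-test version gives 21.6, so 22. Power at 22 is 0.918 (normal) or 0.905 (t).
- The printed formula, without squares on SD and effect, gives 20.8 with SD 352, because 352/355.5 is close to 1. With the listed S of 3.52 it gives 0.2, so 3.52 cannot be the value used.

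The 22 is thus reproduced from the stated figures on the raw score at one time point, which is neither a transformed score nor a change.

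**2. What the same inputs give on other scales.**

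- *Log score, one time point.* CV = 352/2370 = 0.149; log-SD = √ln(1 + 0.149²) = 0.148. A ratio of 1.15 needs 24 per group (power 0.88 at 22); a ratio of 0.85 needs 18 (0.95).
- *Absolute change.* SD = 352 × √(2(1 − ρ)). The protocol gives no correlation ρ between the two scores. Assumed ρ of 0, 0.3, 0.5 and 0.7 give 42, 29, 21 and 13 per group, with power at 22 of 0.66, 0.81, 0.92 and 0.99.
- *Log change, ratio 1.15.* Assumed SDs of 0.2, 0.3 and 0.5 give 44, 97 and 269 per group, with power at 22 of 0.64, 0.34 and 0.15.

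**3. Power by scale when the true effect is multiplicative.** Simulation with 22 per group, a true ratio of 1.15 and a lognormal baseline with mean 2370. The SD of log change is set so that the normal formula returns 90%: ln(1.15) × √(22/2) / (1.96 + 1.2816) = 0.143. Only the first CV comes from the protocol.

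| Baseline CV | Log change, baseline-adjusted | Absolute change, baseline-adjusted |
|---|---|---|
| 0.149 (from 4.4) | 87-88% | about 87% |
| 0.5 (assumed) | 87-88% | 81% |
| 1.0 (assumed) | 87-88% | 67% |
| 1.5 (assumed) | 87-88% | 56% |

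**4. Equal relative progression, unequal baselines.** Both cohorts progress by 50%, and one starts 25% lower (assumed). At the mean, the absolute changes are 0.5 × 2370 = 1185 and 0.5 × 0.75 × 2370 = 889, a difference of about 296 units with no difference in percentage progression. Absolute change without baseline adjustment is declared different in about 56%, 27% and 11% of simulated studies at CV 0.15, 0.5 and 1.0 (another run gave 52%, 28% and 12%). With the baseline score as covariate, on either scale, the rate is 5-6%.

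**The case against.** Several stronger readings are tempting, and the text does not support them.

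- A reader might take 7.1.1 to define an absolute, untransformed change. It is a bare label that names no scale and is compatible with the transformation in 4.4.
- A reader might take 9.2 to make relative change the outcome. It appears there only as the reason for the baseline correction.
- A reader might take 9.1 to plan an unadjusted comparison of absolute change. It states neither, so step 4 shows what would follow if the gap were filled that way, not what the protocol plans. Those rejections are also not false positives on the absolute scale, where the cohorts truly differ; they show that the question answered depends on the scale.
- A reader might conclude that the stated 90% power is not reached. That is not established. At the protocol's own CV of 0.149 the choice of scale costs almost nothing, and absolute change has power 0.92 if ρ is 0.5.

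It is also fair that the exact transformation and the handling of zero scores commonly belong in an analysis plan, and that adjusting for baseline is sound whatever reason is given for it.

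What stands is the conflict between sections. A CV of 0.149 also sits poorly with a score that 9.1 says "is a continuous variable with a skewed distribution", so larger CVs deserve to be considered. And the one stated correction belongs to risk-factor analyses that do not list modality.

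**Conclusion.** The point holds as an internal contradiction. The protocol gives the primary outcome no single scale or model, calls the change in score primary in 7.1.1 and secondary in 9.2, and does not state baseline correction for the comparison that answers the primary objective. The 9.2 rationale is backwards.

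The size depends on how skewed the score is. At the protocol's CV the loss of power from using baseline-adjusted absolute change is negligible. At CVs of 0.5 to 1.5 it falls to between 81% and 56%, against 87-88% for log change. These figures rest on a lognormal baseline, a multiplicative effect and an SD of log change chosen to match 90%; the protocol gives none of these. The result for unequal baselines applies only if absolute change is compared without baseline adjustment.

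**What to change.** - In 4.4, 7.1.1 and 9.1, make the primary cohort comparison a linear regression of change in the transformed score, with the transformed baseline score as covariate. Use the same wording in the Summary.
- Choose a transformation that is defined at 0, since the eligibility criteria set no minimum score and relative change is undefined for a baseline of 0.
- Use the same outcome in 9.2 and 9.3, and call it primary there.
- Make the three-category multinomial model in 9.1 secondary.
- Replace the reason in 9.2 with: absolute change depends on the initial score.
- State in 4.4 that 22 per group and 90% power refer to the raw score at one time point, not to the transformed change, for which the protocol gives no SD.

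The cost is wording. The baseline scan is already scheduled at inclusion, so no new data are needed. There are two downsides. A transformed change is less direct to read, so report it back-transformed as a percentage difference. And the protocol can no longer claim 90% power for the primary analysis unless an SD of the transformed change is supplied.

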#### Pulse wave velocity

Pulse wave velocity measurements will be performed at baseline and 1, 2 and 3 years after inclusion. It can be calculated from arterial pulse contours. These are obtained by applanation tonometry (Sphygmo-Cor system, PWV Inc, Sydney, Australia) at the carotid and radial arteries and femoral artery. With this technique the artery is pressed against a hard underground (bone) with a pencil-type probe. The probe contains a strain-gauge transducer at the tip with a small pressure-sensitive ceramic sensor area (Millar Instruments, Houston, Texas, USA). To determine aortic and brachial pulse wave velocity, the distance travelled by the pulse wave over the body surface is measured as the distance between the recording sites at the femoral or radial artery to the suprasternal notch minus the distance from the recording site at the carotid artery to the suprasternal notch, as described by others. The investigation takes about 15-20 minutes.

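### Change in pulse wave velocity is corrected for the baseline of another measurement or for none: 9.2 names only the initial calcification score and the 9.3 covariates omit initial PWV

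*Protocol*

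**What the plan says.** Section 9.2 analyses both changes in one sentence: the relation of the risk factors to "secondary outcomes (change in coronary calcification score, change in pulse wave velocity) will be determined with univariate linear regression analysis". The explanatory variables are "each independent variable (demographic data, calcium-phosphate parameters, inflammation markers and calcification inhibitors"; treatment modality is not among them. The section closes with its only correction, "the results will be corrected for initial calcification score", and the reason it gives concerns how relative change in calcification relates to the starting amount of calcification.

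Section 9.3 repeats the plan for the same two changes ("secondary outcomes (change in coronary calcifications score, change in pulse wave velocity) will be determined with multivariate linear regression analysis") and lists what is adjusted for: "The effects of age, gender, body weight, blood pressure, medication, hemoglobin, lipids, quality-of-life, performance status and medication on the relationship". Neither initial PWV nor the initial calcification score is in that list.

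Section 9.1 extends its three-category multinomial model to PWV ("The same goes for pulse wave velocity of the aorta and iliac arteries") and names no baseline value. Its between-group comparison is stated for calcification only: "The calcification score of the different groups will be compared by regression analyses".

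Baseline PWV is available. Section 7.3 says "Pulse wave velocity measurements will be performed at baseline and 1, 2 and 3 years after inclusion", and the investigations table in section 3 also marks PWV at inclusion. Change in PWV is a secondary endpoint in 7.1.2, although the Summary lists it as the second main parameter.

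**The concern.** The plan accepts that a change should be corrected for its starting value, but applies this to only one of the two changes it models. The phrase about the results can be read in two ways. If it covers both outcomes, PWV change is corrected for a calcification score, which is a different measurement. If it covers calcification only, PWV change has no baseline correction. The 9.3 list does not repair either reading.

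Two things are at stake. First, baseline PWV usually explains part of the variation in PWV change; leaving it out keeps that variation in the residual and widens the intervals for the risk-factor associations. Second, marker levels are not randomised. If patients with high marker levels start with stiffer arteries, part of an apparent association with change may reflect where they started. An analyst following the text would also have to choose between the two readings after the data are in.

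**Working it through.** **Inputs from the protocol.** The target is 22 complete patients in each of four groups, two-sided alpha 0.05, power 0.90 (section 4.4). That target is sized on the calcification score. No SD, correlation or sample size is given for PWV.

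**The plan's own figure.** Difference = 0.15 × 2370 = 355.5, SD 352. Normal approximation: 2 × (1.96 + 1.28)² × (352/355.5)² = 20.6, so 21 per group. With the t distribution, power is 0.891 at 21 and 0.905 at 22, so 22 reproduces. It says nothing about PWV.

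**Precision.** Assume equal SD σ at baseline and follow-up, correlation r between them, and a risk factor unrelated to baseline PWV.

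- Residual variance of change without baseline PWV: 2σ²(1 − r).
- Residual variance with baseline PWV as covariate: σ²(1 − r²).
- Ratio, adjusted to unadjusted: (1 + r)/2.
- Standard error without baseline relative to with it: √(2/(1 + r)).

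| Assumed r | Variance ratio | SE without baseline | Effective number out of 4 × 22 = 88 |
|---|---|---|---|
| 0.5 | 0.75 | +15% | 66 |
| 0.6 | 0.80 | +12% | 70 |
| 0.7 | 0.85 | +8.5% | 75 |
| 0.8 | 0.90 | +5% | 79 |

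Outside this range, the SE is 24% larger at r = 0.3 and 3% larger at r = 0.9. The last column is 88 × (1 + r)/2. It supposes that the risk-factor models pool all four cohorts, which the protocol does not state.

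**Confounding by baseline.** Suppose two sets of patients, for example with high and low marker levels, differ by 0.5 SD in baseline PWV, and there is no true effect on change. If follow-up regresses on baseline alike in everyone, the unadjusted difference in change is −(1 − r) × 0.5 SD, which is −0.25 SD at r = 0.5 and −0.15 SD at r = 0.7. A simulation with 22 per set (4,000 runs) checked this case and the opposite one, in which each set is stable around its own mean.

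| Situation | r | Unadjusted change | Adjusted for baseline |
|---|---|---|---|
| Common regression on baseline | 0.5 | −0.248 SD | 0.002 SD |
| Common regression on baseline | 0.7 | −0.152 SD | −0.002 SD |
| Each set stable around its own mean | 0.5 | 0.004 SD | +0.257 SD |
| Each set stable around its own mean | 0.7 | 0.000 SD | +0.153 SD |

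Adjustment removes bias in the first situation and introduces a bias of the same size in the second (Lord's paradox). The precision result does not settle which situation applies.

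**The case against.** **The protocol is silent rather than wrong.** Nothing in it forbids using baseline PWV. The reason attached to the correction in 9.2 points to calcification alone, and a covariate for a secondary endpoint is often left to an analysis plan, which is not shown here. This has some force. But the protocol did not leave the PWV models open: it names a correction in the section that models PWV change and lists covariates for PWV change explicitly. A list that is given and omits the outcome's own baseline is a specification that needs repair.

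**Adjustment is not always right in a cohort.** This stands. The simulation shows that either analysis can be the biased one, so the argument for baseline PWV rests first on precision and on clear wording. It is also why both analyses should be reported.

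**The size is assumed and modest.** This also stands. At r of 0.7 or more the SE penalty is 8.5% or less, on an endpoint that did not drive the sample size. If the risk factor is correlated with baseline PWV, the gain from adjusting is smaller.

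**Stronger readings that the documents do not support.** A reader might infer that the omission biases the comparison of treatment modalities, since patients choose their modality and PWV is not a matching factor. But the models in 9.2 and 9.3 concern risk factors, and section 9 states a group comparison for calcification only.

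A reader might also calculate an inflated type I error. With an assumed SD of 3 m/s and 22 per group, a 1 m/s baseline difference shifts the change by (1 − r) m/s against an SE of 3 × √(2(1 − r)) × √(2/22), giving 8.6% at r = 0.5 and 6.4% at r = 0.8. Those figures require a true population gap of 1 m/s, for which the protocol gives no evidence. A chance imbalance is already contained in the variance of the change, and the overall error stays at 5.0%. Given an observed chance imbalance of 1 m/s, the conditional SE uses √(1 − r²) and the error is 5.4% (r = 0.5) to 5.2% (r = 0.8).

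**Conclusion.** The point holds as a defect of specification. Read either way, 9.2 leaves change in PWV without a correction for its own starting value, and 9.3 does not supply one. The main consequence is lost precision in the risk-factor models: standard errors about 5% to 15% larger for an assumed correlation of 0.8 to 0.5, with equal variances and a risk factor unrelated to baseline PWV. Confounding by baseline stiffness is possible but conditional on common regression on baseline. No claim about bias between modalities or about an inflated error rate follows. The calcification endpoint is affected only in that 9.3 does not repeat its correction. This is a cheap improvement to a secondary analysis and does not threaten the primary one.

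**What to change.** Reword the closing sentence of 9.2 so that each change is corrected for its own initial value: calcification change for the initial calcification score, PWV change for initial PWV of the same arterial segment. Carry both corrections into the 9.3 list, and state whether they also apply to the PWV model in 9.1. Name the segment, because 7.3 describes aortic and brachial PWV whereas 9.1 refers to the aorta and iliac arteries.

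Report the models of PWV change without the baseline covariate as a prespecified sensitivity analysis. State that, in this non-randomised cohort, the two may differ and that the choice between them rests on whether patients regress on baseline alike.

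The cost is a sentence in each section, one extra analysis and a conditional interpretation. No new measurement, visit or change in sample size is needed.
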